We will exclude older adults with a pre-treatment SS of less than 8 from this study. For each older adult, we will select the most hypersensitive tooth (the highest SS) due to exposed root surface for the assessment of dentine hypersensitivity in follow-up visits. A dental periodontal graduated probe at the nearest mm will measure the maximum amount of gingival recession of the selected hypersensitive tooth. The same trained examiner will perform the clinical examination and assessment of dentine hypersensitivity immediately after treatment and at 4-week and 8-week follow-up visits, using the same tools and procedures as in the baseline examination. We will re-examine 10% of the older adults later on the same day to assess the intra-examiner agreement at the baseline and follow-up examinations. To promote the follow-up rate, a research assistant will remind all older adults of their follow-up appointment schedule. If they are absent at the follow-up visit, another timeslot will be provided within the same week.

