### 4.10. Outcome Measure

The primary outcome will be the change in dentine hypersensitivity of the most hypersensitive tooth in response to compressed air blast stimuli. This will be measured as the change in SS from the baseline visit to the 8-week follow-up visit after the intervention, to evaluate the anti-hypersensitivity effect of SDF and potassium nitrate solution.

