### 4.11. Sample Size Calculation

Based on a previous clinical trial [8], we estimate that the percentage of change in SS in the test and positive control groups will be 52% and 40%, respectively, with a common standard deviation of 22% and 23%, respectively [8]. Using a power of 0.8 and a statistical significance of 0.05, the minimum number of older adults needed for the study with a dropout rate of 10% was calculated to be 148, with 74 older adults per group, which was determined via the Mann–Whitney test using the software G*Power 3.1 (Franz Faul, Kiel University, Kiel, Germany) [26].

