### 4.13. Data Analysis

We will apply the statistical software SAS for Windows (SAS Institute Inc., Cary, NC, USA) and SPSS for Windows (IBM Corporation, Armonk, NY, USA) for data analyses. The data will be assessed for a normal distribution using the Shapiro–Wilk test for normality. A chi-squared test will be used to determine the difference in distribution of gender and tooth type between the 2 groups. A Mann–Whitney U test will be used to study the pre- and post-treatment SS and the reduction in SS of the treatment group if these data are not normally distributed, whereas a t-test will be used instead if these data are normally distributed. We will report the medians and interquartile ranges for all of the continuous variables to provide information on the data distribution. All statistical tests will be 2-tailed, and the significance level will be set at 0.05. This study will use the intention-to-treat principle for analysis. However, if the number of older adults who withdraw from the study is significantly different between test and positive control groups at the 8-week follow-up visit, we will use a per-protocol approach for analysis and only older adults who have completed the 8-week follow-up will be included in the results. We will also study independent variables, such as demographic background and VPI, which may modify the treatment effect.

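### The named efficacy tests use neither baseline SS as a covariate nor the week-4 SS, and the article does not say how participants without a week-8 score enter the intention-to-treat analysis (optional improvement)

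*Protocol article*

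**What the plan says.** Section 4.10 defines the primary outcome: "This will be measured as the change in SS from the baseline visit to the 8-week follow-up visit after the intervention". Section 4.6 schedules SS readings before treatment and then "immediately after treatment and at 4-week and 8-week follow-up visits".

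Section 4.13 names the efficacy tests. For non-normal data, "A Mann–Whitney U test will be used to study the pre- and post-treatment SS and the reduction in SS of the treatment group"; the alternative is that "whereas a t-test will be used instead if these data are normally distributed". It then states: "This study will use the intention-to-treat principle for analysis". If withdrawals differ significantly between arms at week 8, the plan moves to a per-protocol analysis in which "only older adults who have completed the 8-week follow-up will be included in the results". One further analysis is mentioned without a method: "We will also study independent variables, such as demographic background and VPI, which may modify the treatment effect".

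Section 4.11 sizes the trial on the Mann–Whitney test, expecting reductions of 52% and 40% with SDs of 22% and 23%. With power 0.8, significance level 0.05 and 10% dropout, it arrives at 74 per group, 148 in total.

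**The concern.** The trial will hold up to four SS readings per participant, but the efficacy tests named compare two groups on one quantity at a time. Baseline SS enters only through subtraction, and the week-4 reading has no stated part in the week-8 comparison.

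Two things are at stake. One is precision: baseline and week-4 SS both carry information about week-8 SS, and using them costs nothing. The other is selective loss. Participants with little relief at week 4 are plausible leavers. If leaving depends on week-4 SS, poorer responders are lost more often from the weaker arm, and a comparison of those remaining understates the difference. A model that includes the week-4 score corrects this as long as dropout depends on recorded scores. A two-sample test on observed week-8 change cannot.

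This applies in the default branch, where intention-to-treat is declared. The switch to completers is a separate matter.

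**Working it through.** **1. The plan's sample size.** Inputs from section 4.11; two-sided testing from section 4.13.

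- Pooled SD = √((22² + 23²)/2) = √506.5 = 22.51; d = 12/22.51 = 0.533.
- Two-sided Mann–Whitney power by the A.R.E. method (noncentral t, n scaled by the minimum A.R.E. of 0.864): 65 per arm gives 0.7998 and 66 gives 0.806, so 66 are needed.
- 66/0.9 = 73.3, rounded up to 74 per arm, or 148. This matches exactly.

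So the plan already allows for 74 − 66 = 8 participants per arm without a usable score. With all 74 observed, power would be 0.849.

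**2. Precision available from week 4 alone.** If 8 of 74 per arm lack week 8 but all have week 4, with correlation ρ between the readings, the effective number per arm is

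n_eff = 1 / (ρ²/74 + (1 − ρ²)/66).

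For ρ = 0.7: 1/(0.49/74 + 0.51/66) = 69.7. The documents give no ρ, so a range is shown, with power on the same A.R.E. basis:

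| ρ (assumed) | n_eff | Power, all leavers have week 4 | Power, half have it |
|---|---|---|---|
| 0.3 | 66.6 | 0.810 | 0.808 |
| 0.5 | 67.8 | 0.817 | 0.811 |
| 0.7 | 69.7 | 0.827 | 0.817 |
| 0.9 | 72.3 | 0.841 | 0.824 |

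Against 0.806, the gain is 0.2 to 3.5 points. This is precision only, without baseline adjustment or selective dropout.

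**3. Simulation with selective dropout.** From the plan: 74 per arm, week-8 reductions 52% v 40%, SDs 22% and 23%, 10% dropout. Assumed: baseline SS 8 to 10, whole-number scores, week-4 reductions 42% v 32%, correlation 0.5 to 0.7, and all dropout after week 4 by a logistic rule on week-4 SS, the same in both arms. Trials with significantly different withdrawal (Fisher p < 0.05) were discarded, so only the default branch is examined. The model estimate combines a regression of week-8 SS on arm, baseline and week-4 SS with the arm effect on week-4 SS.

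- Dropout unrelated to SS: no bias. Power is about 0.82 to 0.83 for Mann–Whitney and 0.865 to 0.88 for the model, a gain of about 4 to 5 points. One run put it at 3 to 4.
- Strong dependence (log-odds 0.8 per SS point), arm difference in SS points:

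| Correlation | Full data | Completers | Model | Power, Mann–Whitney v model |
|---|---|---|---|---|
| 0.5 | 1.052 | 1.012 | 1.043 | 0.799 v 0.844 |
| 0.7 | 1.036 | 0.977 | 1.027 | 0.767 v 0.847 |

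For correlation 0.7, completers are low by 1 − 0.977/1.036 = 5.7% and the model by 1 − 1.027/1.036 = 0.9%. The power gap is 8.0 points. A repeat run gave 0.792 v 0.866, a gap of 7.4 points.

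**4. Where the gain comes from.** In that repeat run, a baseline-adjusted model on completers had power 0.821. So 0.821 − 0.792 = 2.9 points come from baseline adjustment and the parametric test, and 0.866 − 0.821 = 4.5 points from week 4.

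**The case against.** The strongest objection is that most of this lies in what the article leaves unsaid. It does not say that the intention-to-treat analysis omits participants without a week-8 score. A reader might infer that, but the contrast with a completers-only fallback suggests the default set is wider, and either named test can be run on imputed scores. A condensed article may leave missing-data rules to a fuller document, so the silence alone is no error. This stands.

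A reader might also infer that testing is confined to one visit and that week-4 scores are ignored. The text does not support this: section 4.13 covers post-treatment SS without naming a visit, so week-4 scores may well be tested. What remains is that no named method lets them inform the week-8 comparison.

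It might further be thought that the trial is underpowered. It is not on the plan's own reckoning, since 148 already allows for 10% loss.

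The bias is small and conservative. At its largest above it is 1.036 − 0.977 = 0.059 points. With a change SD of about 0.225 × 9 = 2.03 points (baseline of 9 assumed), the standard error on 66 per arm is about 2.03 × √(2/66) = 0.35, so the bias is about one-sixth of it. It works against silver diamine fluoride, not for it. The dropout mechanism is assumed, and placing all loss after week 4 favours the model. The simulation also used a two-step estimate without the immediate reading, not the full repeated-measures fit.

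These points limit the size of the concern. They do not remove it: the article fixes an unadjusted test where a better one is available from data and software already in the plan.

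**Conclusion.** The point holds as an optional improvement. The named tests leave baseline and week-4 information unused in the week-8 comparison, and they need a week-8 score that the article gives no means of supplying. The stated sample size stands, with power 0.806 on 66 per arm.

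At 10% dropout and correlations of 0.5 to 0.7, the gain is about 4 to 5 power points when dropout is unrelated to SS, part of it from baseline adjustment and the parametric test. It rises to about 8 points under strong dependence on week-4 SS, where a bias of roughly 1 to 6% towards no difference is also mostly removed. The gain is smaller if some participants leave before week 4. The correlation, week-4 means and dropout rule are assumptions, so the direction is firmer than the exact size.

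**What to change.** In section 4.13, make the primary analysis a prespecified repeated-measures model of post-treatment SS (immediate, week 4, week 8). Include arm, visit, arm-by-visit, baseline SS and baseline-by-visit, with unstructured covariance. Include every randomised participant with at least one post-treatment SS, and report the week-8 arm difference with its 95% confidence interval. Keep the Mann–Whitney test on observed week-8 change as a sensitivity analysis.

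The cost is a few sentences and a few lines of code in SAS or SPSS, both already named. No new data, visits or participants are needed. The downside is that the model treats a bounded 0 to 10 score as continuous and assumes dropout depends on recorded scores, which is why the rank test is worth keeping.

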### 4.7. Intervention

After the baseline or follow-up clinical examinations, the eligible older adults will receive either 38% SDF solution (Saforide 38%, Morita, Osaka, Japan) or 5% potassium nitrate solution (Potassium Nitrate, Sigma-Aldrich, Darmstadt, Germany) on the exposed root surface of the selected hypersensitive tooth. If the adjacent tooth or teeth are also hypersensitive, the adjacent tooth or teeth will also receive therapy. An independent operator will dry the selected hypersensitive tooth and use a micro-brush to apply either 38% SDF solution or 5% potassium nitrate solution for 60 s [25], according to the assigned treatment group, on the exposed root surface. The SDF and potassium nitrate will be applied at baseline and at the 4-week follow-up visit after clinical examination. All eligible older adults will receive dietary advice, standardised oral hygiene instruction, a toothbrush and a regular fluoridated toothpaste (1450 ppm) after baseline examination until the end of the study period. We will instruct all older adults not to eat or drink for 30 min after SDF or potassium nitrate application. Because a dentist will professionally apply the intervention, there will be no concern regarding adherence to the intervention for both groups. Applying SDF or potassium nitrate solution will not affect the participants’ usual care pathways, such as medication use. They are prohibited from receiving other dental treatments for dentine hypersensitivity during the study period. In addition, they must follow the oral hygiene instruction received at the baseline visit.

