### 4.9. Blinding

The examiner and the participating older adults will be blinded to the group allocation throughout the study. An independent operator will apply SDF or potassium nitrate solution after clinical examination. If the older adult requests the treatment history, unblinding is allowed. An unblinded research assistant will disclose treatment allocation to that older adult, who will then be excluded from the study.

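### Section 4.13 replaces intention-to-treat with a completers-only analysis when withdrawals differ between arms, which is when a completers-only comparison is most at risk of bias

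*Protocol article*

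**What the plan says.** Protocol article, section 4.13 (Data Analysis), sets the default: "This study will use the intention-to-treat principle for analysis". The next sentence makes it conditional. The condition is "if the number of older adults who withdraw from the study is significantly different between test and positive control groups at the 8-week follow-up visit"; the consequence is "we will use a per-protocol approach for analysis and only older adults who have completed the 8-week follow-up will be included in the results".

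This wording makes completers-only a replacement for intention-to-treat, not an additional analysis. No other section keeps intention-to-treat as primary once the condition is met. The section names no test for comparing withdrawals, only a general two-sided 0.05 level.

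The rule governs the primary outcome, which section 4.10 defines as "the change in SS from the baseline visit to the 8-week follow-up visit after the intervention". Section 4.9 adds another route to loss after randomisation, for a participant who asks what treatment was given: "An unblinded research assistant will disclose treatment allocation to that older adult, who will then be excluded from the study".

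**The concern.** A completers-only comparison is safe when those who leave are unrelated to outcome, or leave both arms in the same way. A clear imbalance in withdrawals is the most visible evidence against that. The sound response is to hold on to the randomised groups and examine how far the missing scores could alter the result. Section 4.13 does the reverse and restricts the analysis to those who stayed.

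If poor responders leave one arm more than the other, that arm looks better than it is. Depending on which arm loses them, this produces a false advantage or hides a real one. Informative loss is plausible here: the outcome is self-rated pain, participants may withdraw at any time, and other treatment for hypersensitivity is prohibited during the study, so someone without relief has a reason to leave.

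The rule also leaves the primary analysis set undecided until the withdrawal counts by arm are known.

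**Working it through.** **Inputs from the protocol article.** Section 4.11: "we estimate that the percentage of change in SS in the test and positive control groups will be 52% and 40%, respectively"; SDs 22% and 23%; power 0.80; alpha 0.05; 10% dropout; 74 per arm. Sections 4.13 and 4.15-style details needed here are only the two-sided testing (4.13) and the 1:1 ratio (4.8). Points below are percentage points of SS change, the scale of section 4.11.

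**Step 1: the plan's own figure.** Pooled SD = √[(22² + 23²)/2] = 22.5, so d = 12/22.5 = 0.533. A two-sided Mann–Whitney calculation with the minimum asymptotic relative efficiency (0.864) needs 66 per arm (power 0.806). Then 66/0.9 = 73.3, rounded up to 74 per arm, 148 in total. The stated size reproduces.

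**Step 2: when the switch fires (74 per arm, two-sided 0.05).**

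| Fewer withdrawals | Fires from, chi-squared (uncorrected) | Fires from, Fisher |
|---|---|---|
| 0 | 4 | 6 |
| 3 | 10 | 11 |
| 4 | 12 | 13 |
| 5 | 13 | 14 |
| 7 | 16 | 17 |

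For 4 against 12, p = 0.034 by uncorrected chi-squared and 0.061 by Fisher, so the unnamed test can decide the primary analysis.

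| True withdrawal | Fires, chi-squared | Fires, Fisher |
|---|---|---|
| 5% vs 20% | 82% | 75% |
| 5% vs 15% | 55% | 44% |
| 10% vs 10% | 5% | 3% |

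**Step 3: bias among completers, no true effect.** Assumptions: 20% leave one arm and 5% the other; the tendency to withdraw has correlation λ = 0.7 to 0.8 with poor week-4 response; week-4/week-8 correlation 0.7. With normal scores, the completers' mean in an arm with withdrawal p is shifted by SD × 0.7 × λ × φ(z_p)/(1 − p).

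- p = 0.20: φ/(1 − p) = 0.280/0.80 = 0.350
- p = 0.05: φ/(1 − p) = 0.103/0.95 = 0.109
- 20% arm = control (SD 23): 23 × 0.7 × 0.350 × λ = 5.64λ
- 5% arm = test (SD 22): 22 × 0.7 × 0.109 × λ = 1.68λ
- False difference = 3.96λ: 2.8 points at λ = 0.7, 3.2 at λ = 0.8

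Expected completers are 74 × 0.80 ≈ 59 and 74 × 0.95 ≈ 70, so the SE is √(23²/59 + 22²/70) = 3.99. A shift of 2.8 to 3.2 is 0.70 to 0.80 SE, which gives a two-sided rejection rate of about 0.11 to 0.13. Simulation with the Mann–Whitney test also gives 0.11 to 0.13. A regression on week-4 response that uses all randomised participants gives about 0.1 point and 0.05. With λ = 0.5, completers show about 2 points and 0.08.

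**Step 4: planned effect, losses in the control arm.** At λ = 0.8 the completers' estimate is 12 − 3.2 = 8.8. Then 8.8/3.99 = 2.21, giving power of about 0.60; simulation gives 8.7 to 8.8 and about 0.61. The week-4 model recovers about 12 with power of about 0.86.

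**Step 5: where the result changes.**

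- Withdrawal unrelated to response: no bias and type I error of about 0.05, even at 5% vs 20%.
- Withdrawal of 5% vs 15%, which averages to the planned 10%, and driven directly by outcome (logistic slope −1 to −2 per SD): 2.0 to 2.8 points, type I error 0.08 to 0.10.
- Withdrawal of 5% vs 20% driven by the week-8 response (λ = 0.7 to 0.8): completers' type I error 0.18 to 0.22; the week-4 model still has 0.09 to 0.12.
- In the outcome-driven simulations, restricting to trials in which the switch fired barely changes the completers' figures (at 5% vs 20%, 0.10 against 0.11 for slope −1, and 0.19 in both cases for slope −2).

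**The case against.** Four points on the other side have force.

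First, a reader might infer that completers-only is necessarily most biased when withdrawal is unequal. The documents do not support that. Unequal loss unrelated to response causes no bias, and equal loss for different reasons in each arm can cause it. Imbalance is a warning sign, not proof.

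Second, a reader might take the 3 points as the effect of the switch itself. The article does not say how a missing week-8 score is handled under intention-to-treat, which may properly sit in an analysis plan that is not shown. If the default were an available-case test, participants without a week-8 score would drop out either way and the same bias would arise. The figures compare completers with one reasonable model that the protocol does not name. What remains is that the rule, once triggered, rules out any analysis of all those randomised.

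Third, 5% vs 20% is an assumption. The protocol gives only 10% overall dropout, in an eight-week trial with appointment reminders and same-week rescheduling. With equal 10% withdrawal the switch fires in only 3% to 5% of trials.

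Fourth, a reader might go on to say that the replacement set is not truly per-protocol, or that section 4.7 is wrong that "there will be no concern regarding adherence to the intervention for both groups". Neither is established. Completing week 8 can be read as a condition added to a per-protocol definition given elsewhere. The adherence remark rests on professional application of the agent; it is loose, because the second application needs attendance at week 4, but it has no bearing on the switch.

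**Conclusion.** The rule is wrong as written and should be changed. It is an explicit instruction, so an unseen analysis plan does not excuse it, and it can determine the headline result. The defect is the conditional replacement of intention-to-treat, made on post-randomisation data and triggered by the main sign of informative loss.

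The size is illustrative. It rests on assumed withdrawal rates, an assumed link between withdrawal and week-4 response, and the 0.7 correlation. Under these, the false difference is about a quarter of the planned effect (3/12), and control-arm losses would lower power from about 0.86 to 0.61. A weaker link gives less, and no link gives none.

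**What to change.** In section 4.13:

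- Delete the conditional switch.
- State that all randomised participants, analysed as allocated, form the primary analysis whatever the withdrawal pattern.
- Use baseline and week-4 SS for missing week-8 SS, for example by multiple imputation or a repeated-measures model. The choice of method can be left to the analysis plan.
- Add a delta-adjusted sensitivity analysis, because a week-4-based model reduces but does not remove bias if withdrawal depends on the week-8 response.
- Report completers or per-protocol results as supportive only.

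The sample size stays at 148. The cost is rewording and a little more analysis work, with no new participants, visits or data items.

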### 4.14. Ethical Consideration

We sought ethical approval from the local Institutional Review Board (UW22-517). Written consent will be obtained from all participating older adults after explaining the study’s purpose and procedures. All participating older adults will be allowed to withdraw from the study at any time through informing the primary investigator. Withdrawal from the study will not affect their right to receive other dental care, such as oral health education. The study will present a minimal risk to the participating older adults. All the field workers will receive professional training to minimise the risk. We will inform participants via the consent form that if they are harmed by taking part in this clinical trial, no compensation will be provided. If one life-threatening case is found or more than 30% of the participants suffer from severe systemic side effects, this clinical trial will cease immediately. All the personal information about potential and enrolled participants will be confidential in a personal computer with a password, and only the investigators will have access to it.

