## Abstract

Background: Dentine hypersensitivity on an exposed root surface induces pain, affects daily oral hygiene practice, limits dietary choices and negatively affects quality of life. Silver diamine fluoride is marketed in the United States as a desensitising agent, but well-designed clinical trials are limited. This study evaluates the anti-hypersensitivity effect of silver diamine fluoride on hypersensitive teeth due to an exposed root surface in older Chinese adults. Methods/design: We will conduct a randomised double-blind clinical trial with a sample size of at least 148 Chinese older adults aged 65 or above who have dentine hypersensitivity due to an exposed root surface. We will collect written consent before the study. A trained examiner will examine the participants’ teeth with a blast of compressed air from a 3-in-1 syringe. Those adults who report a self-perceived sensitivity score (SS) (0 to 10) of 8 or more on at least one tooth with an exposed root surface will be recruited. The recruited older adults will be randomly allocated into two groups using a block randomisation of six. Group 1 participants will receive the application of 38% silver diamine fluoride solution every 4 weeks. Group 2 participants will receive the application of 5% potassium nitrate solution every 4 weeks. Dietary advice, oral hygiene instruction and fluoride toothpaste at 1450 ppm will be provided to participants in both groups. The same trained examiner will perform follow-up examinations for the participants and determine the dentine hypersensitivity in SS of the most hypersensitive tooth (with the highest pre-treatment SS) immediately after the intervention and at 4-week and 8-week intervals. Discussion: There is no consensus on the standard of care for a professionally applied desensitising agent in older adults. This trial will provide evidence for clinicians to devise an effective dental care plan for older adults with dentine hypersensitivity. Trial registration: NCT05392868 Registered on 22 May 2022.

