### 4.8. Randomisation, Treatment Group Allocation and Allocation Concealment

A research assistant will randomly allocate eligible older adults who have at least 1 hypersensitive tooth with an SS of 8 or more due to exposed root surface into 2 intervention groups with a block randomisation of 6 and with a 1:1 ratio. A statistician will generate a random number sequence in a computer. The 2 intervention groups are as follows:SDF (test) participants will receive topical application of 38% SDF solution on the exposed root surface of the most hypersensitive tooth every 4 weeks;Potassium nitrate (positive control) participants will receive topical application of 5% potassium nitrate solution on the exposed root surface of the most hypersensitive tooth every 4 weeks.

There will be no negative control group for ethical reasons. A research assistant will keep the random number sequence in opaque sealed envelopes and conceal the allocation sequence until interventions are assigned.

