Stimulus-based or response-based assessments can evaluate dentine hypersensitivity [27]. Stimulus-based assessment is performed via applying a stimulus in an intensity to evoke pain, and it is used to measure the pain threshold; response-based assessment is performed by subjectively evaluating the pain stimuli produced, and it is used to estimate pain severity [27]. This study aims to evaluate whether SDF can reduce dentine hypersensitivity; hence, we will utilise a response-based assessment to investigate the change in pain severity that the participants perceive. In the response-based method, the visual analogue scale, numeric rating scale, verbal descriptor scale and faces pain scale are generally used for measurement [30]. Of these, the verbal descriptor scale was recommended as the scale of choice for evaluating pain intensity among older adults [30]. The SS that we will use in this study is modified according to the verbal descriptor scale, with the addition of adjective words representing different levels of pain intensity, so as to enhance the older adults’ understanding [8]. The outcome will be the change in SS from the baseline visit to the 8-week follow-up visit.

Diet and oral hygiene practice will influence dentine hypersensitivity [12]. We will provide all participants with dietary advice and standardised oral hygiene instructions before the intervention, to avoid any modification to the outcome measure. The older adults will receive a clinical examination and compressed cold air test only. Both SDF and potassium nitrate solution have been approved as safe for clinical use, and the related procedure for clinical application is simple and non-invasive. Therefore, this study will have limited ethical concerns. 

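### Apart from the one-case life-threatening trigger, the stopping rule in section 4.14 pools both arms, so severe systemic harm from one agent is diluted by half before it is judged against 30%

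*Protocol article*

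**What the plan says.** Section 4.14 (Ethical Consideration) gives a stopping rule with two limbs joined by "or". It opens "If one life-threatening case is found or more than 30% of the participants" and the second limb reads in full "more than 30% of the participants suffer from severe systemic side effects, this clinical trial will cease immediately". The first limb needs a single case. The second is a share of the participants, with no mention of arm.

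The same section states: "The study will present a minimal risk to the participating older adults". The Discussion (section 5) adds: "Both SDF and potassium nitrate solution have been approved as safe for clinical use".

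The sample size in section 4.11 "was calculated to be 148, with 74 older adults per group"; the Abstract makes this a minimum ("with a sample size of at least 148 Chinese older adults aged 65 or above"). Section 4.8 allocates "with a block randomisation of 6 and with a 1:1 ratio". On exposure, section 4.7 says: "The SDF and potassium nitrate will be applied at baseline and at the 4-week follow-up visit after clinical examination". Section 4.9 keeps the examiner and participants blinded and mentions an unblinded research assistant, whose stated task is to disclose allocation to a participant who asks for it.

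**The concern.** Severe systemic events that are not life-threatening are governed only by the 30% limb. In a 1:1 comparison of two different agents, the harm to plan for is harm from one of them. A pooled share then divides that agent's events by roughly twice the number of people who received it, so the observed rate is about half the rate in the affected arm. The limb can stay silent while a large part of one arm is affected.

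The level itself raises a second question. A section that describes the study as minimal risk also lets dozens of severe systemic events pass before the second limb acts. A reader, or an ethics board, cannot easily hold both statements together without an explanation.

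**Working it through.** **Inputs.** N = 148, 74 per arm (section 4.11); 1:1 in blocks of 6 (section 4.8); threshold strictly above 30% of participants (section 4.14). The one-arm event rates below are illustrative assumptions; the article gives no expected rate of severe systemic effects.

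**Step 1: the plan's own N.** Difference 52 − 40 = 12 points; pooled SD = √((22² + 23²)/2) = 22.51; d = 12/22.51 = 0.533. A two-sided Mann–Whitney test at 0.05 with power 0.80 and minimum asymptotic relative efficiency 0.864 needs 66 per arm. With 10% dropout, 66/0.90 = 73.3, so 74 per arm and 148 in total. The stated figure is reproduced.

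**Step 2: cases needed at full enrolment.** The smallest count above 30% is floor(0.30 × N) + 1. For N = 148, 0.30 × 148 = 44.4, so 45.
- 44/148 = 29.7%: no stop.
- 45/148 = 30.4%: stop.

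Because 148 is a minimum, 45 is the lowest count at full enrolment.

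**Step 3: harm in one arm only.** 45/74 = 60.8% of that arm must be affected, and 44/74 = 59.5% can be affected without a stop. At a true rate of 50% in one arm and none in the other, 0.50 × 74 = 37 events are expected, and 37/148 = 25% pooled. Binomial probability of 45 or more among 74:

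| True rate in the affected arm | Probability that the pooled limb fires, single look at 148 |
|---|---|
| 40% | 0.0002 |
| 50% | 0.04 |
| 60% | 0.49 |

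**Step 4: the reading with participants to date as denominator.** The trigger is then 1 case among the first 1 to 3 participants, 4 of 10, 16 of 50 and 31 of 100. Simulation (20,000 trials, blocks of 6, 50% rate in one arm and none in the other, check after every participant):

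| First participants ignored | Probability that the pooled limb ever fires |
|---|---|
| 0 | 81% |
| 9 | 62% |
| 19 | 50% |
| 39 | 35% |

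Much of the power on this reading comes from small early counts. With a 5% rate in both arms, the pooled limb checked from the first participant stops about 15% of trials.

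**Step 5: the same 30% counted within each arm.** This keeps the plan's threshold and changes only the counting. At 74 per arm, 0.30 × 74 = 22.2, so 23 cases (31.1%). With a 50% rate in that arm, the probability of 23 or more among 74 is above 0.999; with 40% it is 0.96. The price appears early: with a 5% rate in both arms and a check after every participant, a by-arm count stops about 28% of trials if checked from the first participant, and under 1% if checked from about 10 per arm.

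**The case against.** The best objection is that the rule is not only its second limb. One life-threatening case, in either arm and at any point in enrolment, stops the trial. A reader who takes up the text from the 30% onward might infer that no harm can stop this trial before 45 people are affected. That inference is wrong: the bar of 45 applies only to severe systemic events that are not life-threatening, and only at full enrolment. This objection stands, and it limits the point to the second limb.

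Three further objections stand in part.

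- *The 0.04 depends on the denominator.* With participants to date it becomes 35% to 80%, so the pooled limb is not blind on every reading. But even the best of these misses about one trial in five at a 50% one-arm rate, and it reaches that only by acting on the first few participants. The article's silence on denominator and review times is ordinary condensation and is not held against it here.
- *Minimal risk describes expectation; a stopping threshold is a contingency.* Both can be true, so a reader who sees a flat contradiction goes too far. The tension remains and deserves an explanation.
- *Pooling does not produce the 45; the 30% level does.* Correct. Pooling is a separate weakness, which moves the bar from 30% to about 61% for the arm that is harmed.

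A reader might also infer from the two-application schedule that a late stop protects almost nobody. The article does not support this. Recruitment opened on 1 September 2022 and the study was expected to end on 30 April 2023, with 8 weeks of follow-up each, so entry may well be staggered. A stop could then spare later entrants and those still awaiting the week-4 application.

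**Conclusion.** The point holds for the 30% limb only. As worded, that limb pools two arms that receive different agents, so at 148 enrolled it needs 45 cases, equal to 61% of one arm if the other is unaffected. A 50% rate confined to one arm would be caught with probability 0.04 at a single look at 148, and in about 35% to 80% of trials under continuous checking on participants to date. Counting the same share within each arm would catch it almost always. These figures assume 74 per arm, no events in the other arm, and event rates chosen for illustration. The documents give no reason to expect such rates, and the Discussion describes both agents as approved as safe.

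The minimal-risk statement and a limb that lets up to 44 severe systemic cases pass are in tension and need reconciling, short of a strict contradiction.

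**What to change.** 1. The investigators and the ethics board should reconcile the minimal-risk statement with the 30% limb in section 4.14, and keep or set the threshold themselves. No threshold is proposed here.
2. Whatever threshold they choose, section 4.14 should say that the share of participants with severe systemic side effects is counted within each arm as well as overall, by someone who has access to allocation and does not examine participants.

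The cost is a few lines of protocol text and notification of the ethics board. The unblinded research assistant in section 4.9 could do the counting, but that role now covers only disclosure on request and would have to be extended to safety counts. The statistical downside is a higher chance of a false stop while the by-arm denominators are small (Step 5). It is largely a matter of when by-arm checking begins, which the investigators and ethics board should weigh when they agree the wording. The life-threatening trigger is unaffected.
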